## Abstract

**Background:**

Acupuncture, as an important component of traditional Chinese medicine (TCM), has been widely applied in the treatment of chronic insomnia in China, while there is no clinical study related to its therapeutic mechanism.

**Methods/design:**

A single-center, single-blind, randomized, placebo-controlled trial will be conducted at Jiangsu Hospital of Traditional Chinese Medicine. A total of 60 patients will be registered. Eligible participants will be randomly divided into acupuncture group and sham acupuncture group (*n* = 30 cases in each group). Patients in both groups will be treated once every other day, three times per week for 4 weeks. The primary outcome measures are Pittsburgh Sleep Quality Index (PSQI) and concentrations of adrenocorticotropic hormone (ATCH), corticotrophin-releasing hormone (CRH), and cortisol (CORT). Secondary outcome measures are Insomnia Severity Index (ISI) and Fatigue Severity Scale (FSS).

**Discussion:**

This study aims to evaluate the therapeutic effects of acupuncture on chronic insomnia by using PSQI, ISI, and FSS. The mechanism of acupuncture on CIPs will be preliminarily discussed by analyzing the changes in concentrations of CRH, ACTH, and CORT before and after treatment.

**Trial registration:**

Chinese Clinical Trials Register, ChiCTR1800020298.

## Background

Insomnia is a condition of unsatisfactory sleep quality and is associated with daytime functional impairment [1, 2]. Among adults, 6–10% of patients meet the diagnostic criteria for insomnia [3]. Chronic insomnia is a severe sleep disorder. With increasing stress factors, such as working conditions and family and social pressures, the incidence of chronic insomnia is increasing. Chronic insomnia not only causes cardiovascular and psychiatric diseases reducing patients’ quality of life, but also causes high absenteeism and mortality risk, and ultimately leads to increased social burden [4–8].

Drug therapy and psychotherapy are the recommended treatments in current clinical guidelines [9–12]. Benzodiazepine receptor agonists (BZras), the most commonly used drugs for the treatment of insomnia, are effective for short-term treatment of insomnia, while their long-term therapeutic effect is limited [13], and a number of studies have reported that they may cause a great number of side effects [10, 14–19]. Due to concerns related to dependence and side effects, chronic insomnia patients (CIPs) are often eager to choose non-pharmacological treatments [20, 21]. Cognitive behavioral therapy (CBT) as a psychotherapeutic treatment for insomnia has been proven to be effective [2]. Due to lack of professionals and expensive treatments, however, CBT isn’t highly beneficial for the majority of patients [22].

Acupuncture, as an important component of traditional Chinese medicine (TCM), has been widely applied to treat a variety of diseases worldwide, especially sleep disturbances and mood disorders [23, 24]. Based on a meta-analysis, acupuncture has a superior therapeutic effect than benzodiazepines in the treatment of primary insomnia [25]. Although acupuncture is effective in the treatment of chronic insomnia, it still lacks standardized clinical studies and its therapeutic mechanism has remained elusive, restricting its clinical application.

Chronic insomnia is closely associated with an irregular sleep–wake rhythm. To explore the mechanisms of insomnia, the root causes of insomnia need to be studied further. In recent years, there have been several mainstream trends in the study of mechanisms of insomnia: dysfunction of the hypothalamus-pituitary-adrenal (HPA) axis, decline in the melatonin system function, neurotransmitter disorders, etc. [26–29].

Studies showed that stress is one of the important causes of insomnia. For individuals under chronic stress, first their amygdala will be activated, leading to activation of the HPA axis and increased secretion of CORT. Then, the concentrations of ACTH and CORT will increase, resulting in an awakening effect. Therefore, insomnia is closely associated with dysfunction of the HPA axis [30, 31]. Previous animal experiments confirmed that acupuncture is effective in regulating the level of HPA axis-related hormones [32, 33], although a limited number of clinical studies have been conducted.

## Methods/design

### Hypothesis

Based on the validity of acupuncture in treating insomnia, we hypothesize that acupuncture will improve the symptoms of CIPs, and there will be a difference between acupuncture and sham acupuncture based on the points of PSQI and concentrations of ATCH, CRH, and CORT.

### Objectives

The purpose of this study is to determine whether the mechanism of acupuncture in treating chronic insomnia is related to the HPA axis. By comparing changes in concentrations of ATCH, CRH, and CORT before and after treatment, this study is expected to verify the validity of this inference and provide a scientific basis for the therapeutic mechanism of acupuncture in treating chronic insomnia.

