### Outcome measures

#### Primary outcome measures

PSQI is a questionnaire for assessment of individuals’ sleep quality comprising seven parts, such as sleep quality, time to fall asleep, sleep time, sleep efficiency, sleep disorders, the taking of sleeping pills, and daytime dysfunction. The total score of PSQI is 0–21 and is inversely proportional to sleep quality; the higher the PSQI score is, the worse the sleep quality is. PSQI > 5 can be a reference threshold to judge sleep quality. In the present study, PSQI > 5 will be taken as the inclusion criterion for chronic insomnia. PSQI will be evaluated before treatment and after 4 and 8 weeks of treatment.

For determining concentrations of ACTH, CRH, and CORT, 4 ml of venous blood will be drawn and anticoagulant will be added. Plasma will be separated by centrifugation at 3000 rpm and then stored in a refrigerator (− 70 °C). A Beckman automatic chemiluminescence enzyme free analyzer (Beckman Coulter, Inc., Brea, CA, USA) will be used for the determination. Two venous blood samples from each participant will be taken at 8 am on the day before the treatment and 8 am on the day after the end of the final treatment.

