### Statistical analysis

In this study, SPSS 22.0 software (IBM, Armonk, NY, USA) will be used to analyze the data. The measured data will be expressed as mean ± standard deviation, and the count data will be expressed by the ratio or composition ratio. For comparing measured data between the two groups, first normal analysis will be performed. A *t*-test will be used for the measured data conforming to normal and homogeneity of variance, and a non-parametric rank sum test will be used for non-normally distributed measured data. The data will be counted by the chi-square test or Fisher’s exact test. *P* values ≤ 0.05 will be considered statistically significant.

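### The Objectives say a before-after hormone comparison will verify an HPA-axis mechanism, but the planned two-group tests can show only whether acupuncture alters these hormones relative to sham

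*Protocol article*

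**What the plan says.** The Objectives open with the trial's purpose: "The purpose of this study is to determine whether the mechanism of acupuncture in treating chronic insomnia is related to the HPA axis". The next sentence names the means: "By comparing changes in concentrations of ATCH, CRH, and CORT before and after treatment, this study is expected to verify the validity of this inference". The Discussion paragraph of the abstract describes the same means, "by analyzing the changes in concentrations of CRH, ACTH, and CORT before and after treatment", but promises only a preliminary discussion of mechanism.

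Two other sections describe a different comparison. The Hypothesis is that "there will be a difference between acupuncture and sham acupuncture based on the points of PSQI and concentrations of ATCH, CRH, and CORT". The Statistical analysis section begins "For comparing measured data between the two groups, first normal analysis will be performed" and continues "A *t*-test will be used for the measured data conforming to normal and homogeneity of variance", with a rank sum test for non-normal data. No section states a hypothesis or an analysis that joins a hormone to PSQI.

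On timing, the primary outcome section says "Two venous blood samples from each participant will be taken at 8 am on the day before the treatment" and again on the day after the last session. Table 1 places the second hormone measurement and a PSQI assessment at the same post-treatment visit, with a further PSQI assessment at 8 weeks. The Sample size section rests on PSQI alone.

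**The concern.** Two things are out of line.

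First, the comparison is described in two ways. The Objectives and the abstract speak of change before and after treatment; the Hypothesis and the Statistical analysis speak of a difference between groups. Only the second is protected by randomisation. Change within one arm also contains time, regression to the mean and placebo response.

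Second, even the between-group comparison does not answer the question in the Objectives. A hormone difference between arms shows that acupuncture changes the hormone. It does not show that the change in the hormone produces the change in sleep. Both could follow from treatment separately, or better sleep could itself change the hormones.

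At stake is the main conclusion. Because mechanism is the stated purpose, a significant hormone result alongside a significant PSQI result could be published as verification of the HPA hypothesis when the data cannot bear that claim.

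**Working it through.** The plan gives no figure for the mechanism question, so there is none to reproduce. The check compares the sections and then asks how well the planned tests separate a true HPA mechanism from its absence.

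**1. What the sections deliver**

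| Section | Comparison | Links hormone to PSQI? |
|---|---|---|
| Abstract, Discussion | before-after hormone change | no |
| Objectives | before-after hormone change | no, but claims verification of mechanism |
| Hypothesis | acupuncture vs sham, PSQI and each hormone | no |
| Statistical analysis | two-group t-test or rank sum test | no |

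**2. Inputs.** From the Sample size section: 60 patients, 30 per arm, 15% dropout. Completers: 60 × 0.85 = 51, or 30 × 0.85 = 25.5 per arm (25 used). Significance level 0.05 from Statistical analysis. Assumed, because the document does not give them: two-sided tests, and a standardised effect of 0.8 on one hormone and on PSQI.

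**3. Do the planned tests separate the two explanations?** A two-sample t-test with 25 per arm and an effect of 0.8 SD has power of about 0.79.
- Hormone has no influence on PSQI: the tests are independent, so both are significant with probability 0.79 × 0.79 ≈ 0.63. Simulation gives 63%.
- Hormone carries 80% of the PSQI effect (PSQI = 0.8 × hormone − 0.16 × arm + residual, total effect −0.64 − 0.16 = −0.80): simulation gives 71%.

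The ratio is 0.71 / 0.63 ≈ 1.13. Under these assumptions, a double positive is almost as likely without the mechanism as with it.

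**4. Does the between-group test control for a shared fall?** Yes. With the same true fall of 0.4 SD in both arms and 25 per arm, a two-group test of change scores is significant in 5.1% of simulated trials, which is the nominal rate.

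**5. What could a hormone-PSQI analysis add?** For a correlation adjusted for arm in 51 completers, the standard error on Fisher's z scale is 1/√(51 − 4) = 0.146. The correlation detectable with 80% power is tanh((1.96 + 0.84) × 0.146) ≈ 0.39.

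Such an analysis would not settle direction. Suppose sleep drives the hormone and there is no HPA mediation: PSQI effect 0.8 SD, within-arm correlation 0.6 (assumed), 25 per arm. The hormone effect is then 0.6 × 0.8 = 0.48. Adjusting PSQI for the hormone removes 0.6 × 0.48 = 0.288, and 0.288 / 0.8 = 36% of the effect. The association is significant in over 99% of simulated trials. This would look like mediation although none exists.

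**The case against.** The strongest reply is that the design is sounder than the Objectives suggest. The Hypothesis, directly before the Objectives, specifies acupuncture versus sham, and the Statistical analysis plans a two-group test. Read together, comparing changes before and after treatment may simply mean comparing changes between arms. This stands. A reader might infer that a significant fall within the acupuncture arm is the planned test and that false verification would be frequent. The documents do not support that: no paired or within-arm test is planned, and the two-group test holds its nominal error rate (step 4).

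A second tempting reading is that the hormone data cannot support the mechanism at all. That also goes too far. A randomised hormone difference is indirect evidence, and a clear absence of one would count against the hypothesis. The article is more cautious elsewhere: the abstract promises only a preliminary discussion, and the main Discussion speaks of an initial validation and calls for further confirmation in a larger sample.

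A third reply is that a correlation or mediation analysis usually belongs in the analysis plan or full protocol, neither of which is shown. This is right, so its absence is not counted as a fault here. It does not answer the point, because the Objectives themselves name the hormone comparison as the means of verification. The cautious wording elsewhere conflicts with that sentence and does not remove it.

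Finally, an arm-adjusted association cannot exclude that better sleep changed the hormones (step 5). That stands too, and is why the association is offered only as an optional, exploratory addition. The 8-week PSQI, collected after the second hormone sample, gives a better time order but still does not prove direction.

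**Conclusion.** The point holds in a limited form. The Objectives promise more than the planned analysis can give: separate two-group tests can establish that acupuncture alters ACTH, CRH or CORT relative to sham, but not that its effect on sleep runs through them. The Objectives and abstract also describe a before-after comparison where the Hypothesis and Statistical analysis describe a between-group one.

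This conclusion follows from the text and needs no assumed figure. The 63% and 71% show its size under an assumed effect of 0.8 SD on both measures and 25 completers per arm; other effects would change both percentages. The fault is in the inference, not in the validity of the hormone test. It deserves correction because mechanism is the trial's stated purpose.

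**What to change.** 1. Align the Objectives and the abstract with the Hypothesis. State that each hormone is compared between acupuncture and sham at post-treatment, adjusted for its baseline value (for example ANCOVA, on the log scale if skewed), and that before-after change within an arm is not evidence of effect. Baseline adjustment uses data already collected. With baseline-to-post correlation ρ and equal variances, its variance is proportional to 1 − ρ², against 1 for post-treatment values alone and 2(1 − ρ) for change scores. It exceeds neither, since 2(1 − ρ) − (1 − ρ²) = (1 − ρ)² ≥ 0.

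2. Replace the claim of verification with an aim such as *to assess whether acupuncture alters HPA-axis hormones compared with sham*. Limit a positive conclusion to *consistent with an HPA pathway*.

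3. Optionally, prespecify an arm-adjusted analysis of hormone change against PSQI change, including PSQI at 8 weeks, with confidence intervals. Label it exploratory and hypothesis-generating, and state that it cannot settle direction and, with about 51 completers, has 80% power only for a correlation of about 0.39.

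No new visits, samples or patients are needed. The cost is a more modest headline claim and slightly more analysis work. Recruitment had already begun when the article was submitted, so the change should be dated and made before unblinding.

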### Design

In this study, 60 patients will be selected from January 2019 to December 2020 who are admitted to Jiangsu Hospital of Traditional Chinese Medicine (Nanjing, China). A single-center, single-blind, randomized, placebo-controlled trial will be conducted to compare the efficacy of acupuncture and sham acupuncture in the treatment of CIPs. Both groups will be treated once every other day, three times per week for a total of 4 weeks. The clinical trial complies with the 2010 Consolidated Standards of Reporting Trials (CONSORT) guidelines [34] as well as the Standards for Reporting Interventions in Controlled Trials of Acupuncture (STRICTA) [35]. Figure 1 shows the trial’s procedure and Table 1 details the trial’s schedule.

**Fig. 1 Fig1:**
[figure not shown]
Trial procedure

**Table 1 Tab1:** Schedule of enrolment, interventions, and assessments

	Baseline	Intervention		P-T	F-U
	-1 week	0 day	4 weeks		8 weeks
Enrolment					
Eligibility screen	X				
Informed consent	X				
Medical history	X				
Physical examination	X			X	X
Allocation	X				
Intervention					
Acupuncture group (*n* = 30)		12 sessions of acupuncture in acupoints			
Sham acupuncture group (*n* = 30)		12 sessions of acupuncture with no skin penetration			
Outcomes					
PSQI, ISI, FSS	X			X	X
CRH, ACTH, CORT	X			X	
Others					
Success of blinding				X	
Adverse events check		X	X	X	X

*PSQI* Pittsburgh Sleep Quality Index, *ISI* Insomnia Severity Index, *FSS* Fatigue Severity Scale, *CRH* corticotropin-releasing hormone, *ACTH* adrenocorticotropic hormone, *CORT* cortisol, *P-T* post-treatment, *F-U* follow-up

### Patients

#### Recruitment strategies

There are three main approaches for recruiting patients with chronic insomnia: 1) patients admitted to the outpatient clinics of the Acupuncture and Moxibustion Department and Neurology Department of Jiangsu Traditional Chinese Medicine will be potential participants; 2) publicity brochures will be distributed in the halls of Jiangsu Hospital of Traditional Chinese Medicine to recruit potential eligible research subjects; 3) sleep-related popular science articles will be periodically published on the WeChat platform, with a brief introduction of the experimental study, to attract insomniacs to contact and participate. All participants will contact the evaluator by telephone to make an appointment for the evaluation time.

#### Inclusion criteria

Patients meeting all of the following criteria will be enrolled in the study:
Aged 18–65 yearsMeeting International Classification of Sleep Disorders-Third Edition (ICSD-3) diagnostic criteriaPittsburgh Sleep Quality Index (PSQI) score > 5 pointsNot receiving psychotropic medicationNo communication and cognitive impairmentSigns written informed consent form

#### Exclusion criteria

Patients meeting any of the following criteria will be excluded from the study:
Diseases associated with the HPA axis (pituitary tumors, adrenal hyperplasia, etc.)Sleep disorders caused by an organic disease (epilepsy, diabetes mellitus, cardiovascular diseases, renal failure, etc.)Sleep disorders caused by mental illness, such as depression, anxiety disorder, schizophrenia, etc.Diagnosis of other sleep disorders (e.g., obstructive sleep apnea, rapid eye movement sleep behavior disorder, or restless legs syndrome)Drug and alcohol addictsPregnant women, breastfeeding women, and others who are inappropriate to undergo acupuncture treatmentSubjects who underwent acupuncture for insomnia in the past month

### Intervention

Both groups will be treated by experienced acupuncturists with master’s degrees in medicine and doctors legally practicing medicine. All physician assistants will receive one-day professional training to familiarize them with the treatment options.

### The acupuncture group

The acupuncture points are based on *National Standard of China: Meridian Points* (GB12346–90). Participants will be in the supine position and the physician will select a 0.30 × 40 mm disposable sterile acupuncture needle produced by Suzhou Medical Products Factory Co. Ltd (Suzhou, China). The acupuncture depth is at the range of 5–10 mm after routine disinfection and acupoint selection is DU20 (Baihui), DU24 (Shenting), EX-HN3 (Yintang), HT7 (Shenmen), SP6 (Sanyinjiao). The angle and depth of needling will take the standard of each acupoint into consideration. After participants experience a needling sensation (Deqi sensation), a low-frequency pulse electro-acupuncture therapeutic apparatus (XS-998B04; Nanjing Xiaosong Medical Instrument Research Institute Co. Ltd, Nanjing, China) will be connected to the needle handle of DU20 and EX -HN3 and set to a continuous wave at a frequency of 2 Hz. The intensity of the stimulus will depend on the participant’s tolerance and stimulation will be continuous for 30 min. All acupuncture procedures will be performed by the same acupuncturist.

### The sham acupuncture group

In the sham acupuncture group, we will use a non-invasive placebo needle—a 0.30 × 25 mm blunt-headed placebo needle produced by Suzhou Huatu Medical Devices Co. Ltd. (Suzhou, China). Non-invasive placebo needles have been commonly used as placebo controls for acupuncture trials and have been recognized as a reliable sham acupuncture control tool. The acupoint selection will be the same as in the acupuncture group. A low-frequency pulse electro-acupuncture therapeutic apparatus will be connected to the needle handle of DU20 and EX -HN3, while the stimulation intensity button will not be activated. The needle will be removed after 30 min. All sham acupuncture procedures will be undertaken by the same acupuncturist.

### Outcome measures

#### Primary outcome measures

PSQI is a questionnaire for assessment of individuals’ sleep quality comprising seven parts, such as sleep quality, time to fall asleep, sleep time, sleep efficiency, sleep disorders, the taking of sleeping pills, and daytime dysfunction. The total score of PSQI is 0–21 and is inversely proportional to sleep quality; the higher the PSQI score is, the worse the sleep quality is. PSQI > 5 can be a reference threshold to judge sleep quality. In the present study, PSQI > 5 will be taken as the inclusion criterion for chronic insomnia. PSQI will be evaluated before treatment and after 4 and 8 weeks of treatment.

For determining concentrations of ACTH, CRH, and CORT, 4 ml of venous blood will be drawn and anticoagulant will be added. Plasma will be separated by centrifugation at 3000 rpm and then stored in a refrigerator (− 70 °C). A Beckman automatic chemiluminescence enzyme free analyzer (Beckman Coulter, Inc., Brea, CA, USA) will be used for the determination. Two venous blood samples from each participant will be taken at 8 am on the day before the treatment and 8 am on the day after the end of the final treatment.

#### Secondary outcome measures

Sleep severity index scale (ISI) is a self-rating scale designed by Morin and Espie (1993) [36] to evaluate the subjective feelings of individuals with insomnia. The scale includes seven items and each question has a high score of 5 points. Questions 1–3 assess the severity of insomnia and questions 4–7 assess the individual’s sleep satisfaction and daytime impact of and attention paid to insomnia. Participants will complete the questionnaire according to their sleep status in the past week. The higher the score is, the more serious the insomnia degree is. The score ranges from 0 to 28: 0–7 points indicate no problem, 8–14 points represent insomnia, 15–21 points indicate moderate insomnia, and 22–28 points demonstrate severe insomnia. Additionally, ISI will be evaluated before treatment, after 4 weeks of treatment, and after 8 weeks of treatment.

The Fatigue Severity Scale (FSS) was developed by the American Medical Association in 1989 to evaluate various chronic diseases and fatigue symptoms. This includes nine items mainly assessing the impact of fatigue on daily functions, asking about the relationship between fatigue and motivation, physical strength, working condition, family and social life, as well as scoring participants’ fatigue susceptibility and impact. The score ranges from 1 (completely disagree) to 7 (completely agree). The higher the score is, the more serious the fatigue degree is. FSS will be investigated before treatment, after 4 weeks of treatment, and after 8 weeks of treatment.

